**Trial design**

Patients will be divided into two groups. One group with low stage ovarian cancer, and one group with high stage ovarian cancer. All patients in both groups will be administered ICG during at start of the surgery.

During surgery imaging with a NIR fluorescence camera system will be performed at different time points. After resection, NIR fluorescence imaging of the resected tissue will be performed at the pathology department.

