With modern imaging techniques, such as CT and MRI, preoperative localization and staging of tumors can be done reasonably well. However, preoperative imaging and gynecological examination alone are not sufficient in estimating whether a complete or optimal debulking can be carried out. Therefor in the Netherlands, it is currently investigated whether a preoperative laparoscopy can contribute to a better distinction between patients eligible for primary debulking and patients eligible for neo-adjuvant chemotherapy followed by interval debulking in advanced ovarian cancer.(3)

In patients with low stage ovarian cancer, detecting occult metastases has major implications for the treatment, as treatment of patients with metastasised disease involves chemotherapy after the surgical resection.(4)

In order to detect these metastases a staging surgery is performed. This involves taking biopsies of any adhesions surrounding the (area of the) primary tumour, all macroscopic suspect areas, blind biopsies of amongst others the peritoneum, and lymph node sampling. (www.oncoline.nl/epitheliaal-ovariumcarcinoom)

A recent development is the use of fluorescence imaging to visualize also tumors during surgery. This technique makes use of special fluorescent dyes, in combination with NIR light. This NIR light is not visible to the human eye, but can be detected with a camera system. The advantages of this technique are that it does not involve the use of harmful radiation, yet has a penetration depth of approximately 1 cm in tissue. One of the fluorescent dyes which is currently approved for clinical use is ICG. ICG is considered safe for use in humans and has been clinically used since the nineteen fifties for liver function tests and retinal angiography. Moreover, ICG has already been used in image-guided surgery research into detection of the sentinel node in breast, vulva and liver tumors with NIR fluorescence.(5)

Because in vivo ICG binds to serum proteins, it behaves as a macromolecule in the circulation. It is known that macromolecules accumulate in tumor tissue due to increased vascular permeability and reduced drainage in these tissues. This is known as the "enhanced permeability and retention" (EPR) effect.(6;7) In previous clinical trials in breast and gastric cancer patients it was possible to distinguish tumor tissue from the surrounding tissue using ICG in combination with optical imaging.(8-13)

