### Sample size

In this phase 2 pilot study, the value of NIR fluorescent imaging in detection of peritoneal, omental and retroperitoneal ovarian metastases after ICG injection will be studied. Because this study was designed as a pilot study no formal sample size calculation could be performed. Based on the heterogeneity of ovarian cancer metastases in the daily clinic, we expect a total of 15 patients will need to be enrolled. With this sample size we should be able to make a reasonable estimate of the feasibility of the detection of ovarian cancer metastases with NIR fluorescence imaging and ICG. If negative results are seen in all patients, we will consider stopping the pilot study prematurely.

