## Study design

All patients diagnosed with stage IIb t / m IIIc ovarian cancer eligible for debulking surgery will be included. In addition, all patients diagnosed with stage I or IIa ovarian cancer eligble for a surgical staging procedure will be enrolled.

All patients (n = 15) will be administered ICG (20 mg) during the surgery. Intraoperative NIR fluorescence imaging findings will be compared with clinical findings by the gynecologist during the surgery.

During the surgery, standard procedure will be followed and biopsies of clinically suspected areas will be obtained. Additional NIR fluorescent spots, that were not detected by the gynaecologist with usual visual/tactile methods, will also be removed and sent to the pathology department for histopathological assessment. Immediately after the resection, the resected tissue specimens will be transported to the pathology department of the LUMC, where specimens will be photographed and additional NIR fluorescent imaging will be performed. Hereafter the department of pathology’s standard procedure for assessing the resected specimens will be followed for both specimens detected under usual methods and specimens detected under NIR fluorescence imaging.

When it is decided by the attending gynaecologist to also perform a laparoscopic staging (whether or not in the context of the LAPOVCA study), a laparoscopic intra-operative NIR fluorescence imaging system can be used. (See umbrella protocol P10.001 protocol, version 3.0, Appendix 4 and 5 for a detailed description of the laparoscopic camera system).

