**Stage IIb to III ovarian cancer scheduled for debulking surgery**

**Stage I and IIa ovarian cancer scheduled for surgical staging procedure**

**In-/exclusion criteria**

**I.V. injection Indocyanine green**

**NIR imaging**

**Resection by gynaecologist**

**Resection specimen to pathology department**

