## End points

**Primary End Point**

The primary endpoint is the percentage of peritoneal, omental or retroperitoneal ovarian cancer metastases identified with NIR fluorescence imaging (defined as the part of the pathology proven ovarian cancer metastases that also show NIR fluorescence)

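### In the staging group, the choice of blind-biopsy and node sites is not kept independent of the NIR image, which leaves the detection percentage open to upward bias

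*Protocol*

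**What the plan says.** The primary endpoint is a sensitivity, "defined as the part of the pathology proven ovarian cancer metastases that also show NIR fluorescence" (End points). Its denominator is whatever metastatic tissue reaches histology and proves positive.

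The Study design section gives two routes to histology during surgery:

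- The conventional route: "During the surgery, standard procedure will be followed and biopsies of clinically suspected areas will be obtained". The Introduction describes staging surgery for low-stage disease as covering adhesions around the primary tumour, macroscopically suspect areas, and "blind biopsies of amongst others the peritoneum, and lymph node sampling". It also describes removal of uterus, adnexa and omentum in low-stage disease.
- The NIR route: "Additional NIR fluorescent spots, that were not detected by the gynaecologist with usual visual/tactile methods, will also be removed".

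On timing, the boxes of Figure 1 run from ICG injection to NIR imaging and then to "Resection by gynaecologist". The Summary is looser: "During surgery imaging with a NIR fluorescence camera system will be performed at different time points". Neither place says when the blind-biopsy or node sites are chosen, or whether the person choosing them has seen the NIR image.

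**The concern.** To estimate sensitivity, the reference-standard sampling should not depend on the test result. Lesions that are seen, felt or fluorescent are all removed. A metastasis that is neither visible, palpable nor fluorescent is proven only if it happens to lie in tissue taken for another reason. In peritoneum and retroperitoneal nodes, that tissue is largely the blind biopsies and the sampled nodes.

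No visible lesion dictates where a blind biopsy goes, so its position is the step most open to influence by a fluorescence map already in view. If placement drifts towards fluorescent tissue, fewer NIR-negative metastases are proven, the denominator shrinks and the percentage rises. The error can only favour the technique. It bears most on the question posed under Hypothesis / aim, which concerns clinically low-stage patients. Analysis cannot repair it, because unsampled tissue has no histology.

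**Working it through.** **No figure to reproduce.** The plan gives no expected detection percentage. Its total of 15 patients has no calculation behind it ("Because this study was designed as a pilot study no formal sample size calculation could be performed") and is not in dispute here. The check is therefore a reading of the text followed by an illustration.

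**Reading.**

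1. Figure 1, in the order of its boxes, has NIR imaging before resection.
2. The Study design section keeps standard procedure, so blind biopsies and node sampling still take place in the staging group.
3. No sentence fixes their sites before imaging or keeps the image from the person choosing them. The reference to spots missed by usual methods implies a separate conventional assessment but sets no order.
4. The sites may therefore be chosen with the image in view. The text neither requires this nor prevents it.

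**Illustration.** None of these inputs is in the documents; all are assumptions.

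- S: true sensitivity, equal in visible and occult lesions (0.50 or 0.70).
- s: share of metastases that are occult (0.1 to 0.5).
- q: chance that an occult NIR-negative metastasis is sampled when sites are independent of NIR (0.05 to 0.5).
- f: 1 if sites are independent of NIR, 0 if sampling is steered wholly away from NIR-negative tissue.

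All visible lesions and all fluorescent lesions are taken to be proven. Then

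expected estimate = S / [S + (1 − s)(1 − S) + s(1 − S)·q·f].

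Worked example with s = 0.3, S = 0.70, q = 0.2:

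- f = 1: 0.70 / (0.70 + 0.21 + 0.018) = 0.70 / 0.928 = 75.4%
- f = 0: 0.70 / (0.70 + 0.21) = 0.70 / 0.91 = 76.9%

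| s | S | q | f = 1 | f = 0 | Due to steering (points) |
|---|---|---|---|---|---|
| 0.1 | 0.70 | 0.05 | 72.1% | 72.2% | 0.1 |
| 0.3 | 0.70 | 0.05 | 76.5% | 76.9% | 0.4 |
| 0.3 | 0.70 | 0.20 | 75.4% | 76.9% | 1.5 |
| 0.5 | 0.50 | 0.50 | 57.1% | 66.7% | 9.5 |

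Differences are taken before rounding. The first and last rows are the extremes of the ranges tried.

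**Occult lesions only (s = 1).** The formula becomes S / [S + (1 − S)·q·f], and f = 0 always gives 100%. With independent sites:

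- S = 0.70, q = 0.05: 0.70 / 0.715 = 97.9%
- S = 0.70, q = 0.20: 0.70 / 0.76 = 92.1%
- S = 0.50, q = 0.50: 0.50 / 0.75 = 66.7%

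The gaps to 100% are 2.1, 7.9 and 33.3 points. They are upper bounds, because they assume complete steering and ignore the omentum, which is removed whatever NIR shows.

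**Bias without steering.** In the second row of the table the true value is 70%, yet independent sites already give 76.5%. Sparse sampling accounts for about 6.5 points and steering adds about 0.4.

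**The case against.** The strongest reply is that the plan already protects standard sampling. Standard procedure is followed and fluorescent spots are removed in addition, not in exchange. The surgeon has little reason to spend a blind biopsy on a fluorescent spot that will be removed anyway. Figure 1 is a schematic for both groups, its box concerns resection and not choice of sites, and imaging takes place at several time points. All this stands as a reason not to assume that steering will happen. It does not settle where blind samples are placed or what the surgeon has seen by then.

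Three stronger readings are tempting and should not be drawn:

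- *That blind biopsies and nodes are the only histology from NIR-negative, normal-looking tissue, and that it has lost its independence.* The omentum is an endpoint site that is not chosen from the NIR image. Uterus, adnexa and biopsies of adhesions also supply histology. Independence is unsecured, not shown to be lost.
- *That a patient could be understaged.* This presupposes reduced standard sampling, whereas the text keeps it and adds tissue.
- *That the detection percentage could go from 62.5% (10/16) to 100% (10/10).* Such counts assume that every proven metastasis is occult and every relevant sample is diverted. The endpoint counts all proven metastases. With an assumed 64 visible lesions added, 40 of them fluorescent, the same complete diversion moves 50/80 = 62.5% to 50/74 = 67.6%.

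Scope is also limited. Blind biopsies and node sampling are described only for staging surgery, in an unstated share of 15 pilot patients.

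**Conclusion.** The concern holds in a limited form. For the staging group, the protocol does not keep the choice of blind peritoneal biopsy sites and sampled nodes independent of the fluorescence image. These samples matter to the denominator, and any steering would bias the endpoint upward.

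The documents do not give the size. Under the assumptions above it is about 0.1 to 10 points on the overall endpoint, with the upper end reached only when half of the metastases are occult, half of the occult NIR-negative ones would otherwise be sampled, and steering is complete. It could be larger if only occult lesions in low-stage patients are counted. The change is worth making because it is cheap and cannot be made afterwards, not because a large bias has been demonstrated.

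**What to change.** In section 2.4 and Figure 1, for the staging group, state that:

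- the blind-biopsy sites and node stations required by standard procedure are chosen and listed before the NIR image is viewed, and are sampled as that procedure already requires;
- the NIR status of each listed site is logged before excision;
- fluorescent spots outside these sites are removed in addition, as the section already provides, and labelled as such;
- the report gives the number of NIR-negative pre-chosen sites that contain tumour.

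This leaves the clinical content of standard procedure unchanged. It costs a sentence or two, one step in the figure, one column on the surgical form and a few minutes in theatre, with no extra patients. The detection percentage may come out lower.

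The change does not remove the bias that arises because NIR-negative, normal-looking tissue is only sparsely sampled. The protocol should acknowledge that as a limit on how the percentage is read.

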### Secondary End Points

- Tumor-to-background ratio between tumor and healthy tissue.
- Number of additional additional peritoneal, omental, retroperitoneal ovarian cancer metastases detected with NIR fluorescent imaging after ICG injection.

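### Bench NIR imaging precedes histopathology, and the protocol does not mask the pathologist or keep tissue sampling independent of the NIR result

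*Protocol*

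**What the plan says.** The Study design section (2.4 in the table of contents) fixes the order of specimen handling. Tissue goes to the pathology department straight after resection, and there "specimens will be photographed and additional NIR fluorescent imaging will be performed". The next sentence reads "Hereafter the department of pathology’s standard procedure for assessing the resected specimens will be followed", and it continues "for both specimens detected under usual methods and specimens detected under NIR fluorescence imaging". The flow chart in Figure 1 shows the same order: specimen to pathology, NIR imaging, histopathology.

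Tissue reaches pathology by two routes. Clinically suspect areas are biopsied as usual. Fluorescent spots that the gynaecologist had not found "will also be removed and sent to the pathology department for histopathological assessment".

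The primary endpoint is a percentage of metastases, "defined as the part of the pathology proven ovarian cancer metastases that also show NIR fluorescence". A secondary endpoint counts the additional "ovarian cancer metastases detected with NIR fluorescent imaging after ICG injection", so the study has to record the route of detection somewhere.

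The protocol does not say who takes or views the bench images, how specimens are labelled, what the pathologist is told, or how the areas to be sectioned are chosen beyond following standard procedure.

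**The concern.** NIR fluorescence is the test under study, and pathology is the reference standard that decides which lesions count as metastases. If the result of the test can reach the person applying the reference standard, the two are no longer independent. Here the bench image is made in the pathology department before the tissue is assessed, and no safeguard is written down.

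The effect would run in one direction. If fluorescence draws attention to certain areas, metastases there are more likely to be sectioned and proven. Dark metastases are more likely to stay undiscovered and so leave the denominator. The percentage rises although the dye performs no better.

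Two features make this worth settling now:

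- It differs from the selection created by removing spots in theatre only because they fluoresced. Influence at the pathology bench would also reach tissue taken out on purely conventional grounds, so limiting the analysis to conventionally detected specimens would not remove it.
- It cannot be repaired in the analysis. A dark focus that was never sectioned leaves no record. Masking and the order of handling are matters of conduct and belong in the protocol, which already sets that order.

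**Working it through.** The protocol gives no figure to reproduce. The sample size of 15 patients comes without a formula ("no formal sample size calculation could be performed"), and the point does not depend on it. The check has two parts.

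**1. What the text does and does not establish**

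| Question | Protocol |
|---|---|
| Does bench NIR imaging come before histopathology? | Yes, in Study design and in Figure 1 |
| Does it take place in the pathology department? | Yes |
| Does pathology set the primary denominator? | Yes, under Primary End Point |
| Is the pathologist masked to the NIR result or the route? | Not stated |
| Is the choice of areas to section independent of the NIR image? | Not stated |
| Are specimens labelled by route on arrival? | Not stated |
| Is the pathologist shown the NIR images? | Not stated |
| Is the same procedure used for both routes? | Yes, the department's standard procedure |

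The first three rows create the pathway for influence. The next four leave it neither closed nor shown to be in use.

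**2. Possible size**

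All inputs here are assumptions. Let

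- s = true share of metastases in the resected tissue that fluoresce;
- a = chance that pathology proves a fluorescent metastasis;
- b = chance that it proves a dark one;
- q = b/a, the relative chance for a dark metastasis.

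Expected observed share = s·a / (s·a + (1 − s)·b) = s / (s + (1 − s)·q).

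For s = 0.50:

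- q = 0.8: 0.50 / (0.50 + 0.50 × 0.8) = 0.50 / 0.90 = 55.6%
- q = 0.5: 0.50 / (0.50 + 0.50 × 0.5) = 0.50 / 0.75 = 66.7%

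| True share s | q = 1 | q = 0.8 | q = 0.5 |
|---|---|---|---|
| 50% | 50% | 55.6% | 66.7% |
| 70% | 70% | 74.5% | 82.4% |
| 90% | 90% | 91.8% | 94.7% |

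With q = 1 there is no bias. For q below 1 the bias is upward. Across these rows it shrinks as the true share rises, from 5.6 to 16.7 percentage points at 50% to 1.8 to 4.7 points at 90%. The number of patients does not enter the formula, so enrolling more would not reduce it.

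Here q is an average over all metastases in the endpoint. Lesions that would be sectioned whatever the NIR image shows, such as separately biopsied suspect areas, pull q towards 1. Small foci inside a large specimen would pull it down if only part of that specimen is sectioned. That partial sectioning is itself an assumption, since the protocol refers only to standard procedure.

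**The case against.** The strongest reply is that the protocol is silent rather than wrong. Imaging tissue before it is cut is a natural order. Imaging in the pathology department is not the same as showing the images to the pathologist. The text prescribes one standard procedure for both kinds of specimen and nowhere says that NIR guides sectioning. The protocol also cites an umbrella protocol, which is not at hand, and the trial is a small pilot.

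Much of this stands, and it rules out three stronger readings that a reader might infer:

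- *Specimens arrive marked by how they were found.* The text names two kinds of specimen only to say that they are handled alike. The secondary endpoint requires the route to be recorded, but not disclosed to the pathologist.
- *The person sampling the tissue has been shown where it fluoresces.* The imaging is described in the passive, with no operator or viewer named.
- *The percentage is grossly inflated.* Large figures need strong assumed steering. For example, a true 40%, with fluorescent foci sectioned 90% of the time and dark ones 20%, gives 0.36 / (0.36 + 0.12) = 75%. That assumes a 4.5-fold gap and concerns small occult foci, whereas the endpoint pools all proven peritoneal, omental and retroperitoneal metastases.

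The rest does not dispose of the point. A common procedure equalises handling between the two kinds of specimen; it does not by itself make the choice of areas within a specimen independent of the image. The umbrella protocol is cited for the laparoscopic camera system, and whether it covers masking is unknown. Pilot status ("this study was designed as a pilot study") excuses imprecision, but a one-sided bias in the estimate the pilot exists to provide is a different matter.

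**Conclusion.** The point holds as a gap in a stated sequence. The test is repeated on the specimen in the pathology department before the reference standard is applied, and nothing in the protocol keeps the second independent of the first. Because pathology sets the primary denominator, any influence on sampling or reading would push the detection percentage upward.

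Whether such influence would occur cannot be told from the document, and its size is unknown. The illustrative range is about 2 to 17 percentage points for a true share between 50% and 90% and a relative chance of 0.5 to 0.8; it is not an estimate for this trial. Since the remedy is cheap and the loss cannot be recovered later, the change should be made. It does not call the design as a whole into question.

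**What to change.** Add to the Study design section:

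1. Specimens go to pathology under neutral numbers that carry the anatomical site but not the route of detection. The study team holds the key.
2. The areas to be sectioned under the standard procedure are marked before whoever samples the tissue views the bench NIR image.
3. The pathologist reports without access to NIR findings.
4. Sections added because of the NIR image are labelled NIR-guided. They still go into the pathology report and the secondary endpoints, but are left out of the primary percentage.

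Bench imaging can stay ahead of cutting; what changes is who sees the image and when. The cost is relabelling and a reordering of existing steps, with no extra reader or procedure. The downside is that the headline percentage will rest on fewer lesions, because metastases found only in NIR-guided sections no longer count in it.

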**Stage IIb to III ovarian cancer scheduled for debulking surgery**

**Stage I and IIa ovarian cancer scheduled for surgical staging procedure**

**In-/exclusion criteria**

**I.V. injection Indocyanine green**

**NIR imaging**

**Resection by gynaecologist**

**Resection specimen to pathology department**

**NIR imaging**

**Histopathological assesment**

*Figure 1. Schematic overview study design*

## Indocyanine green dose

The dose to be used in this study is 20 mg indocyanine green. This amount of indocyanine green will be dissolved in water just prior to administration. The indocyanine green will be administered intravenously by the anesthesiologist during the surgery. The amount of ICG remains well below the maximum daily dose of ICG 5mg / kg (ICG-Pulsion leaflet). Administration will be done in a single bolus. The dose is based on results of preclinical models in which a dose of 3.5 mg / kg was used, keeping in mind that with doses above the 0.5 mg / kg, the number of allergic reactions to ICG increase.(16)

In previous studies regarding optical imaging of tumor tissue with ICG a dose of 0.01 - 0.25 mg/kg ICG was used.(9;10) However, in these studies NIR fluorescence imaging was performed 30 min after injection.

